## Methods

### Objectives

The proposed study is designed to evaluate whether cholecalciferol substitution in vitamin D deficient kidney transplant recipients has beneficial effects upon the post-transplant outcome compared to placebo. As a primary outcome we will evaluate the impact of cholecalciferol on

- graft function (analyzed using glomerular filtration rate calculated with the MDRD formula as well as albuminuria) one year after kidney transplantation

- the incidence of acute rejection episodes within the first year after kidney transplantation, and

- the frequency and severity (analyzed by means of C-reactive protein levels) of infections within the first year after kidney transplantation.

As a secondary objective we will assess whether cholecalciferol substitution influences the common decline of bone mineral density within the first year after kidney transplantation [44] analyzed by means of absolute bone mineral density (g/cm^2^).

Moreover, courses of calcium levels will be observed in order to assess the safety of cholecalciferol administration at 6800 International Units (IU).

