### Randomization and blinding

If all inclusion and none of the exclusion criteria are met and informed consent has been obtained kidney transplant recipients will be included in the study and allocated a randomization number according to a randomization list. Thus, the participant will be randomly allocated to one of the two treatment arms. The random allocation sequence will be computer-generated using the Randomizer for Clinical Trials 1.7.0 developed at the Institute for Medical Informatics, Statistics and Documentation, Medical University of Graz, Austria. Block randomization will be used in order to prevent imbalanced treatment group sizes. We will use blocks of six to which the two treatment modalities will be randomly allocated in the ratio 1:1. To ensure homogenous treatment groups randomization is stratified by 25-hydroxyvitamin D_3 _levels, with one sub-stratum of kidney transplant recipients found to have 25-hydroxyvitamin D_3 _levels between 25 and 50 nmol per liter and another of kidney transplant recipients with 25-hydroxyvitamin D_3 _levels below 25 nmol per liter.

Participants, investigators, and outcome assessors will be blinded to the allocated treatment. Blinding will be ensured by the use of investigational products that are identical in packaging, labeling, appearance, smell, and taste. Unblinding will only occur in case of emergency and at the conclusion of the study. In most cases, however, discontinuing the treatment should be sufficient without the need for unblinding. Access to the randomization list is restricted to the pharmacist involved in the study and a research assistant.

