### Study intervention

Kidney transplant recipients found to have 25-hydroxyvitamin D_3 _levels below 50 nmol per liter and who fulfill all of the inclusion and none of the exclusion criteria will be randomized to receive either oral cholecalciferol therapy (Oleovit^® ^D_3_-drops) or a placebo solution. Treatment starts on day five after kidney transplantation. Cholecalciferol will be administered at a dose of 6800 IU daily over a time period of one year.

The only adverse drug reaction caused by vitamin D_3 _that may occur is the rise in blood levels of calcium. In case of hypercalcemia the dose can be reduced immediately as serum calcium levels are monitored routinely at close intervals (daily within the postoperative hospitalization, i.e. between two and four weeks on average, thereafter weekly until the fourth month after transplantation, and subsequently every two to four weeks depending on post-transplant complications). At serum calcium levels > 2,65 mmol per liter vitamin D_3 _administration will be reduced to 3600 IU per day. If calcium levels persist above 2,85 mmol per liter over a period of four weeks vitamin D_3 _administration will be discontinued and restarted when serum calcium levels declined to ≤ 2,65 mmol per liter with only 3600 International Units per day. If calcium levels remain high this may be attributed to a persistent or transient hypercalcemia due to hyperparathyroidism as transient hypercalcemia is observed in 20–50% in kidney transplant recipients. Thus, the subject will be tested with ultrasound and ^99m^Tc-methoxyisobutyl isonitrile (MIBI) scan. However, these subjects will not be excluded from the study.

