#### Day 1–5

If a kidney transplant recipient is found to have 25-hydroxyvitamin D_3 _levels below 50 nmol per liter information about the VITA-D study, its purpose, putative benefits, and possible risks will be given to the patient and he/she will be invited to participate in the trial. All subjects will be informed that the participation in the trial is voluntary and that the subject may refuse to participate or withdraw from the trial at any time without giving reasons, without loss of benefits. Kidney transplant recipients who do not agree to participate in the study will receive standard care.

Demographic and baseline data will be collected of all participants within the first five days after transplantation (gender, age, body mass index, cause of end stage renal disease, mode of renal replacement therapy, duration on dialysis).

#### Day 5

Kidney transplant recipients who agreed to participate in the study will be randomized to receive either oral vitamin D_3 _therapy or placebo.

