### Statistical analysis

Baseline data will be expressed as mean values ± standard deviation for symmetrically distributed continuous variables, as median and 25th and 75th percentiles for asymmetrically distributed continuous variables, and as absolute and relative frequency for categorical variables.

Serum creatinine values after one year (the primary endpoint) will be compared between the groups by analysis of covariance (ANCOVA), taking into account as covariates creatinine value at randomization, 25-hydroxyvitamin D_3 _at baseline, and variables which, despite randomization, exhibit large group differences at baseline. ANCOVA will also be applied to the area under the curve of repeated measurements on serum creatinine, CRP, and bone mineral density during the first year of follow-up, using the same set of covariates. Categorical variables (number of acute rejection episodes and infections within the first year after transplantation) will be analyzed using χ^2^-test or fisher's exact test, as appropriate.

All analyses will be performed using an "efficacy subset analysis". Patients are included in this analysis if the study medication has been administered for more than seven days.

Moreover, courses of calcium levels will be described. Furthermore, the Bonferroni-Holm correction will be performed to preserve the global significance level of 5%.

Statistical analysis will be performed with SPSS.

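### The only planned analysis set is defined by more than seven days of study drug after randomisation, and no analysis of all randomised patients is planned

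*Protocol article*

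**What the plan says.** The protocol article, Statistical analysis, names one population and gives it full scope: "All analyses will be performed using an 'efficacy subset analysis". It then sets the entry condition: "Patients are included in this analysis if the study medication has been administered for more than seven days". No intention-to-treat, full analysis or safety set appears anywhere in the article, and the Interims analysis section, under which the trial can be stopped early, names no other population.

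Under Study intervention, "Treatment starts on day five after kidney transplantation". Study procedures, Day 5, places randomisation on the same day.

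The outcomes exposed to this rule include those listed as primary under Objectives: graft function at one year, "the incidence of acute rejection episodes within the first year after kidney transplantation, and" infections over the same period. For safety, Objectives states that "courses of calcium levels will be observed in order to assess the safety of cholecalciferol administration". The analysis section returns to this after the subset rule, in a new paragraph: "Moreover, courses of calcium levels will be described". It gives no population for that description.

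**The concern.** Randomisation makes the two groups comparable on the day it is done. A set that requires more than seven days of treatment selects patients on what happens afterwards, during the early postoperative stay. The article itself expects stopping to follow some clinical events. On emergencies, Randomization and blinding says: "In most cases, however, discontinuing the treatment should be sufficient without the need for unblinding". Patients may also withdraw at any time (Study procedures, Day 1–5).

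Patients who leave in that week may well differ in prognosis from those who stay. If they leave at different rates in the two arms, or for different reasons, the retained groups are no longer the randomised ones, and the comparison can be biased in either direction. Their rejections and infections over the whole year are lost as well. With no all-randomised analysis planned, nothing in the report would show whether the selection mattered.

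**Working it through.** **When membership is decided.** Randomisation: day 5. First dose: day 5. More than seven days of treatment therefore cannot be reached before about day 12. The condition is a post-randomisation one.

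**The plan's own figure.** Inputs from Study population and sample size: difference 0.2 mg/dl, SD 0.5, α = 0.05, power 0.80. Two-sided normal approximation:

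n = 2 × (1.96 + 0.8416)² × 0.5² / 0.2² = 2 × 7.849 × 6.25 ≈ 98.1, rounded up to 99 per arm.

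This matches the stated 99. A one-sided test would give 78, so the stated figure is two-sided. With the planned 100 per arm, power is 80.7%. These figures are for serum creatinine, which the sample size and the ANCOVA both use.

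**Bias from the subset.** Let q₁ and q₀ be the proportions excluded in the two arms, and D the amount by which mean one-year creatinine in excluded patients exceeds that in retained patients. In each arm, overall mean = retained mean + q × D. With no true effect the overall means are equal, so the retained means differ by

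bias = (q₁ − q₀) × D.

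If the gap differs between arms, this becomes q₁D₁ − q₀D₀. It is zero when exclusions are balanced in both number and prognosis. Neither q nor D is in the article, so the values below are assumptions. The standard error of the difference is 0.5 × √(1/n₁ + 1/n₀), where n₁ and n₀ are the numbers retained out of 100.

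| Assumed exclusions | Assumed gap (mg/dl) | Bias (mg/dl) | Share of 0.2 target | SE | Type I error |
|---|---|---|---|---|---|
| balanced, same prognosis | any | 0 | 0 | – | 5% |
| 5% vs 2% | 0.5 | 0.03 × 0.5 = 0.015 | about 7% | 0.072 | about 5.5% |
| 8% vs 3% | 1.0 | 0.05 × 1.0 = 0.05 | 25% | 0.073 | about 10.6% |

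For the last row, 0.05 / 0.0728 = 0.687. The chance of exceeding 1.96 is 1 − Φ(1.273) ≈ 0.102, and in the other tail Φ(−2.647) ≈ 0.004.

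**Power, subset against all randomised.** Equal exclusion in both arms is assumed. In the all-randomised column, the otherwise excluded patients are taken to carry no treatment effect, so the difference shrinks to 0.2 × (1 − q).

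| Excluded | Subset | All randomised |
|---|---|---|
| 2% | 80.0% | 79.2% |
| 5% | 78.7% | 76.6% |
| 10% | 76.5% | 72.1% |

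Only one patient per arm is spare (100 against 99), so the subset itself falls below 80% power once exclusions exceed about 2%.

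**The case against.** Patients, investigators and assessors are blinded with identical products, the threshold is only seven days, and patients are usually in hospital for two to four weeks. All of this makes a large difference in exclusion between arms less likely, and few patients may be excluded at all. That stands, and it limits the likely size of the bias. It does not restore the randomised comparison, and it is equally a reason why including these patients would cost little.

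Four stronger readings are tempting, and the article does not support them:

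- **Hypercalcaemia decides who stays in the set.** A reader might infer this. Under Study intervention, a raised calcium first leads to dose reduction, and discontinuation requires four weeks of persistent elevation. A patient managed by that rule is not stopped for calcium within seven days.
- **All rejections and infections in the first treatment week are dropped.** The rule filters patients and not events. A first-week event in a patient who stays on drug is counted; only excluded patients lose their events.
- **The plan expressly restricts the safety analysis.** The set is labelled an efficacy subset, and the calcium sentence is descriptive and names no population. Coverage of calcium follows from the literal scope of the rule and is not stated separately.
- **The trial faces a bias of known size.** Counting exclusions in one arm only, with a 1.0 mg/dl gap (two of the plan's SDs), overstates what can be known. What matters is the difference between arms, and the range starts at zero.

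It could also be said that analysis sets belong in a statistical analysis plan that is not shown. Here, however, the article itself fixes the population for all analyses.

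**Conclusion.** The concern holds in this form: the plan's single analysis set is conditional on exposure after randomisation, and no analysis of all randomised patients is planned. This follows directly from the text. The safety part is less firm: no population for the calcium description is distinguished from the efficacy subset.

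The size of the bias cannot be determined from the article. Under the assumptions above it runs from zero, through 0.015 mg/dl, to 0.05 mg/dl, with type I error from 5% to about 10.6%. The calculation holds the SD of retained patients at 0.5 and uses the same gap in both arms. The point should be corrected before analysis because the rule defines the primary comparison and the article offers no alternative against which to judge it.

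**What to change.** In Statistical analysis, replace the single subset rule with three statements:

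1. The primary analysis includes all randomised patients in the arm allocated, whatever their exposure. Routine creatinine and CRP are used for early stoppers still in follow-up, and the text states how death and graft loss before one year are handled. That rule is needed because routine care gives no interpretable one-year graft creatinine in those patients.
2. The more-than-seven-days subset is kept as a labelled sensitivity analysis.
3. Calcium is described in everyone who took at least one dose.

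For creatinine, CRP and calcium the added burden is small: the article has them measured daily in hospital, and blood is taken at every outpatient visit. There are two costs. If early stoppers carry no treatment effect the difference is diluted: at 5% excluded, power is about 76.6% against 78.7% in the subset. Bone density at five and twelve months is not routine blood work, so those data in early stoppers depend on their attending the study scans.

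### Describing calcium courses alone answers the 6800 IU safety objective weakly, because the dose is cut when calcium rises; threshold crossings and dose reductions should be reported by arm

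*Protocol article*

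**What the plan says.** Under Objectives, the protocol article states that "courses of calcium levels will be observed in order to assess the safety of cholecalciferol administration" at 6800 IU. The matching sentence under Statistical analysis is that "courses of calcium levels will be described". It names no event, no summary measure and no contrast between the arms. The same section names between-group methods for the other outcomes: ANCOVA for creatinine, CRP and bone mineral density, and a chi-squared or Fisher test for rejection and infection. It also restricts all analyses to patients who received study medication for more than seven days.

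Study intervention gives the assigned treatment: "Cholecalciferol will be administered at a dose of 6800 IU daily over a time period of one year". It then makes exposure depend on calcium. Above 2.65 mmol/l, "administration will be reduced to 3600 IU per day". If calcium stays above 2.85 mmol/l over four weeks, treatment stops, and it restarts at 3600 IU once calcium is 2.65 mmol/l or lower. The section adds that "transient hypercalcemia is observed in" 20–50% of kidney transplant recipients, and that subjects whose calcium remains high stay in the study.

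**The concern.** The outcome that is meant to show whether 6800 IU is safe also decides whether a patient continues to take 6800 IU. After the first value above 2.65 mmol/l, later calcium values in an actively treated patient reflect a lower dose or none. If a summary of courses averages over time or over patients, it mixes values at 6800 IU with values after a cut. It can then look reassuring even though many more patients in the active arm crossed the threshold and had the dose reduced.

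The background rate adds a second difficulty. With transient hypercalcaemia in 20–50% of recipients, a high count in the active arm cannot be attributed to the drug, and a low one cannot clear it, unless it is set against placebo.

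Much rests on this. Study intervention treats a rise in calcium as the only adverse drug reaction that may occur. The Conclusion makes wider use conditional on there being no relevant disadvantages.

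**Working it through.** **The plan's own figure.** The article gives no figure for calcium. Its sample size concerns creatinine (difference 0.2, SD 0.5, α 0.05 taken as two-sided, power 0.80): 2 × (1.960 + 0.842)² × (0.5/0.2)² = 98.1, rounded up to 99 per group. This agrees with the stated 99 but does not bear on calcium.

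**What each measure reflects under the dosing rule.**

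| Measure | Dose it reflects |
|---|---|
| Calcium course over the year | 6800 IU until the first value above 2.65 mmol/l, then 3600 IU or no drug |
| First value above 2.65 mmol/l | Assigned dose; it precedes any calcium-triggered cut |
| Any value above 2.85 mmol/l | The regimen as given; it may follow a reduction |
| Dose reduction or interruption | The direct consequence of the rule |

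The first crossing of 2.65 mmol/l is therefore free of the feedback, and the course is not. The size of any understatement in the courses cannot be calculated from the article.

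**What a by-arm comparison of events could show.** Inputs:
- n = 100 per arm (Study population and sample size).
- Placebo rate p₀ of 20–50% (Study intervention). The article ties no threshold or time window to that range, so using it as the rate of crossing 2.65 mmol/l is an assumption.
- Two-sided α = 0.05.
- Excesses of 15 and 20 points, chosen for illustration.

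Formulas:
- 95% CI half-width at equal rates: 1.96 × √(2p₀(1−p₀)/100).
- Power (arcsine): Φ(h√(100/2) − 1.96), with h = 2·arcsin√p₁ − 2·arcsin√p₀.

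Worked case, p₀ = 0.40: half-width = 1.96 × √(2 × 0.40 × 0.60/100) = 0.136. For p₁ = 0.60, h = 0.4027, and power = Φ(0.4027 × 7.071 − 1.96) = Φ(0.888) = 0.81.

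| Assumed placebo rate | CI half-width (points) | Power, +15 points | Power, +20 points |
|---|---|---|---|
| 20% | 11.1 | 67% | 88% |
| 30% | 12.7 | 60% | 83% |
| 40% | 13.6 | 57% | 81% |
| 50% | 13.9 | 58% | 83% |

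The lowest power in the table is at a 40% placebo rate, not at either end of the range. A pooled-variance normal approximation agrees with these values to within about one point.

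**Analysis set.** The more-than-seven-days rule is worded to cover every analysis, which includes calcium. A patient who stopped in the first week, for any reason, would not appear in the safety description.

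**The case against.** The strongest reply is that descriptive safety reporting is usual, that this is a short article, and that detailed safety tables commonly sit in a full protocol or SAP not shown here. Nothing limits the description to the active arm. The trial has a blinded, concurrent 1:1 placebo arm and frequent calcium measurements, so courses described by arm would already share the same background. The article says courses, not means, so individual trajectories or exceedances would also fit the word. It also expects that calcium may stay high after a reduction, so courses need not return to normal.

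Much of this stands, and it rules out three stronger readings that a reader might infer:
- That the safety objective cannot be answered. By-arm description would answer part of it, for the regimen as given.
- That the plan leaves the placebo arm unused for calcium. The article names no contrast, but it does not exclude one.
- That the 20–50% rate holds regardless of treatment. The text only reports it for kidney transplant recipients.

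The reply does not remove the mismatch. The article ties the objective to a specific dose and states the analysis as description, while naming between-group methods for its other outcomes. That choice fits poorly with a dose that depends on the outcome. The magnitude figures above measure the precision of the proposed comparison, not a bias in the described courses.

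**Conclusion.** The concern holds in a limited form. Described courses alone reflect a start-and-reduce regimen, may understate the calcium effect of the assigned 6800 IU, and answer the safety objective weakly. The seven-day subset weakens the answer further by omitting early stoppers. The primary result is not affected.

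A by-arm comparison of events would be informative but coarse: a 95% CI half-width of about 11–14 points, and power of about 81–88% for a 20-point excess and 57–67% for a 15-point excess. These figures assume 100 evaluable patients per arm and a placebo crossing rate of 20–50%. They also take it that, because dosing is blinded, the calcium rule triggers in both arms; the article does not say so. Changing the analysis wording is a worthwhile and inexpensive improvement, not a correction on which the trial depends.

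**What to change.** Amend the calcium sentence under Statistical analysis so that, in all patients who took any study drug and by randomised arm, the report gives:
- the proportion with calcium ever above 2.65 mmol/l and ever above 2.85 mmol/l after the first dose;
- the time to the first crossing of each threshold;
- the proportion with a dose reduction or interruption.

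Give risk differences with 95% CIs; no formal test is needed. Keep the described courses as a supplement, and exempt these safety summaries from the more-than-seven-days rule.

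The thresholds are the protocol's own, the calcium values are already collected as routine, and dose changes follow from the stated rule. The cost is analysis wording and a few table rows; the dosing rule is not touched. The drawback is coarse precision, so the text should say that a wide interval including zero is not proof of safety.

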### Interims analysis

An interims analysis will be performed after 6 months of follow-up for every subject. Within this analysis glomerular filtration rates between the two groups six months after transplantation and the incidence of acute rejection episodes within six months after transplantation will be analyzed. In case the interims analysis shows a significant difference between the two groups the study will be discontinued prematurely. The strict significance level of 0.001 for interim analysis requires no modification of the significance level for the main analysis [45]. The interims analysis will not break blinding.

### Approval of the ethics committee and the regulatory authority

The proposed study will be conducted in accordance with the Declaration of Helsinki, the Austrian law and subscribes to the principles outlined in the International Conference on Harmonization on Good Clinical Practice, 2002. Approvals were obtained by the Ethics Committee of the Medical University of Vienna and the Vienna General Hospital (Reference Number 213/2008) and the Austrian regulatory authority (Federal Office for Safety in Health Care, Austrian Agency for Health and Food Safety). Furthermore, the study has been registered in a public clinical trial database (ClinicalTrials.gov NCT00752401).

